### Secondary Outcomes

Several secondary outcomes are characterized from the collected data (Textbox 5). Systemic inflammatory response syndrome (SIRS) is central to the diagnosis of infective complications and is defined as greater than or equal to two of the following conditions: (1) temperature over 38^o^C or below 36^o^C, (2) heart rate greater than 90 beats/minute, (3) respiratory rate greater than 20 breaths/minute or PaCO_2_ level less than 32 mmHg, and (4) white blood cell count greater than 12,000/mm^3^ or less than 4000/mm^3^. Blood test results and temperature are classified using standard reference ranges.

Secondary outcomes.Units of RBC and other blood components transfused during the operative period and postoperative hospital stay are recorded.Cerebral oxygenation during the operative period: NIRS readings are recorded for both groups for comparison. Monitoring starts before preoxygenation and anesthetic induction and continues until the patient leaves the theater.Oxygen delivery and utilization during CPB: serial measurements of oxygen delivery and utilization are collected from the clinical perfusion record.EuroQol EQ-5D-3L (a generic health related quality of life instrument that measures mobility, self-care, usual-care, pain/discomfort, and anxiety/depression): assessed at baseline and at 6 weeks and 3 months after surgery.Length of CICU or high dependency unit (HDU) stay.Length of postoperative hospital stay.Clinical outcomes defined as infectious complications (sepsis and wound infection), stroke (validated by CT scanning), ST elevation myocardial infarction accompanied by troponin >5 ng/mL, postoperative acute kidney injury (defined as AKIN criteria stage 1, 2, or 3 [47]), and respiratory complications (ie, reintubation, ventilation >48 hours, tracheostomy, or acute respiratory distress syndrome).Sepsis is defined when antibiotic treatment is required for suspected infection and the presence of systemic inflammatory response syndrome (SIRS) within 24 hours prior to start of antibiotic treatment. Sepsis occurring postdischarge only contributes if the event results in admission to hospital or death; wound infection is considered in the following scenario: ASEPSIS score >20, sternum, and if applicable, leg and arm. Wounds will be assessed at least once during a participant’s hospital stay. A questionnaire will be administered at 3 months to identify wound infections arising after discharge.For stroke diagnosis, blinded assessment of brain imaging (CT or MRI), in association with new onset focal or generalized neurological deficit (defined as deficit in motor, sensory, or co-ordination functions) will be performed.Cumulative resource use, cost, and cost effectiveness.All-cause mortality within 30 days of surgery.Biochemical markers of organ injury.

The following are measured from venous blood samples taken preoperatively, on return to CICU, and 6, 24, 48, and 96 hours postoperatively: (1) S100/100B (brain), (2) troponin I or T (heart), (3) creatinine clearance derived from serum creatinine (kidney), and interleukins (systemic inflammation). The use of these markers has been described previously [48,49]. Urinary creatinine and electrolytes, urinary microalbumin, neutrophil gelatinase-associated lipocalin (NGAL), interleukin 18 (IL18), liver-type fatty acid-binding protein (LFABP), and kidney injury molecule-1 (KIM-1) [50,51] (markers of tubular and glomerular renal injury) are measured from urine collected for over a 3-hour period (1 sample taken preoperatively and 3 samples taken over the first 2 postoperative days).

### Sample Size

The cognitive outcomes are continuously scaled so target differences can be specified as “standardized differences” (0.2 is small; 0.5 is moderate; and 0.8 is large) [52]. In order to detect a small to moderate target difference with 80% power and 5% significance (two tailed), 200 patients (100 per group) are recruited. Specifically, this sample size allows the trial to detect standardized differences between groups of 0.33 (0.36 at 2.5% significance) in cognitive function (adjusting for baseline) and 0.46 in cost, while allowing for up to 12% dropout across the trial. Correlations between measures are assumed to be 0.5 between baseline and postintervention measures and 0.7 between repeated postintervention measures.

This sample size also allows a standardized difference of 0.3 to be detected for biochemical markers (adjusting for baseline and using 4 repeated measures). With respect to CICU and hospital discharge, the sample size allows a hazard ratio of at least 1.65 to be detected.

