### Primary Outcome

The patient-specific algorithm is designed to both prevent regional (cerebral) hypoxia and reduce the likelihood of a patient having an unnecessary RBC transfusion, compared to the generic algorithm. The primary outcome, cognitive function measured at 3 months after surgery, was chosen to measure the hypothesized benefits of preventing regional (cerebral) tissue hypoxia.

Cognitive function is assessed by a qualified examiner blinded to treatment allocation preoperatively, between 4 and 7 days postoperatively, and again at 3 months. The recommended tests [39] are performed in a fixed order (Textbox 3). In addition, to help interpret the cognitive function data, assessments related to the cognitive testing are carried out for all participants (Textbox 4).

Cognitive domain tests and order.Attention (first trial of the Rey Auditory Verbal Learning Test [RAVLT], and sustained and divided attention; Trail-Making Test parts A and B [40,41])Verbal memory (RAVLT [40,42])Visuospatial (block design from the Wechsler Adult Intelligence Scale-Revised (WAIS-R) test [43])Psychomotor speed (digit symbol test from the Wechsler Adult Intelligence Scale-Revised (WAIS-R) test [43])Executive function/verbal fluency (Controlled Oral Word Association Test [COWAT] [44])Motor coordination (Grooved Pegboard Test, dominant and nondominant hand [40])

Assessments related to the cognitive testing.The Wechsler Test of Adult Reading provides a preoperative measure of intellectual ability [45].Documentation of medications known to interfere with neuropsychological functions (including hypnotics, sedatives, neuroleptics, anxiolytics, antidepressants, and β-blockers) preoperatively, 4-7 days postoperatively, and 3 months postoperatively.Assessment of patient’s current mental health using the General Health Questionnaire (GHQ-30) and Hospital Anxiety and Depression Scale (HAD) [46] preoperatively, 4-7 days postoperatively, and 3 months postoperatively, to take into account the potential interaction between postoperative cognition and mood.

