### Statistical Analysis

The primary and other continuous outcomes are analyzed by regression modeling, transforming logarithmically if required, and jointly modeling baseline values where available using mixed models for repeated measures. Serial CPB oxygen delivery and utilization are compared between the 2 groups to determine whether this is improved using NIRS. Time to CICU and hospital discharge is analyzed by Cox regression.

The findings are reported as effect sizes with 95% confidence intervals. Frequencies of complications, which are too infrequent for the trial to be able to detect differences between groups, are tabulated descriptively in accordance with guidelines for reporting RCTs [53]. Analyses are based on intention-to-treat and are adjusted for center and surgery (valve or CABG and valve). For the study to conclude that the patient-specific algorithm is superior to the generic algorithm evidence of superior cognitive function for at least one domain at the 2.5% level is required (the significance level chosen to reduce the likelihood of a type 1 error, but not to be as conservative as a Bonferroni correction).

Health economic analysis are undertaken by the Health Economics Research Centre, University of Oxford. Analyses are designed and conducted to estimate the costs and likely cost of the alternative approaches identified in this protocol. These analyses help to determine whether there are likely to be improvements in patient health outcomes (such as morbidity through complications) associated with the proposed new algorithm, and whether better use can be made of scarce National Health Service (NHS) resources.

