## Discussion

### Key Changes to the Protocol

There have been changes to the protocol since it was first approved in 2009. The study was designed with co-primary outcomes of cognitive function and infectious complications, to measure both the hypothesized benefits of preventing regional (cerebral) tissue hypoxia and a reduction in unnecessary red blood cell transfusion. Evidence available at that time suggested that RBC transfusion was associated with increased rates of infection. However, the TiTRe2 trial [35] found consistent rates of infection with both liberal and restrictive postoperative transfusion thresholds (92% versus 53% transfused, 25% infection rate in both groups with less than 20% due to sepsis). As a result, infective complications was removed as a co-primary outcome and added as a secondary clinical outcome. Similarly, a cumulative infection score, which we had intended to develop using data from the TITRe2 trial by supplementing data on wound infections with data describing the severity of sepsis was dropped. Instead the occurrence of an infectious complication is reported. There have also been changes to the study biomarkers. Urine levels of LFABP and KIM-1 replaced cystatin C and complement activation in blood samples as more sensitive and specific biomarkers for early detection of glomerular and tubular renal injury. Glutathione-*S*-transferases alpha and pi, novel markers of tubular and glomerular renal injury, were also added but have since been removed after preliminary laboratory test results indicated technical problems with the ELISA kits. The manufacturer was informed of these findings. The blood and urine samples collected were stored for analysis at the end of the trial. The indicated changes have not impacted the integrity of the trial.

The study was initially designed as a single-center study in Bristol. To increase recruitment rates, after 2.6 years, the study was extended to 2 further centers. At the request of the funder, the sample size was reviewed after 100 participants were recruited. The correlation between baseline and postintervention cognitive function was lower than anticipated when the study was planned (0.5 rather 0.7) and there was a higher than anticipated dropout rate early on in the trial (see the following section). To account for these differences, the target sample size was increased from 150 to 200 participants. The target effect size was unchanged.

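### The stated detectable differences in cognition (0.33 at 5%, 0.36 at 2.5%) do not follow from the plan's own inputs for the 3-month primary outcome, where they are about 0.37 and 0.40

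*Protocol article*

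**What the plan says.** The protocol article fixes the primary outcome at a single visit: "The primary outcome, cognitive function measured at 3 months after surgery" (Primary Outcome). The same section schedules cognitive testing before surgery, at 4 to 7 days and at 3 months, so there are two postoperative assessments.

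Under Sample Size, "200 patients (100 per group) are recruited", "with 80% power and 5% significance (two tailed"), and the claim is that "this sample size allows the trial to detect standardized differences between groups of 0.33 (0.36 at 2.5% significance) in cognitive function", adjusted for baseline, with up to 12% dropout. The section adds: "Correlations between measures are assumed to be 0.5 between baseline and postintervention measures and 0.7 between repeated postintervention measures". For the biochemical markers it says that four repeated measures enter the calculation. For cognition it does not say how many do.

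Statistical Analysis describes the model as "jointly modeling baseline values where available using mixed models for repeated measures". It requires superiority in at least one cognitive domain at the 2.5% level before the patient-specific algorithm is declared superior. It does not say that the primary effect is averaged over visits.

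**The concern.** A correlation between repeated postoperative measures affects a detectable difference only if more than one postoperative measure enters the calculation. The primary outcome uses one. If the cognitive figures rest on both visits, they describe a more precise quantity than the declared primary outcome, and the stated 80% power does not belong to that outcome.

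This matters most at the 2.5% level, because that is the level at which superiority is decided. A null result would be read against a claimed 20% chance of missing a true difference of 0.36 in a given domain. If the figure does not hold at 3 months, that chance is nearer 30%.

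**Working it through.** **Inputs** (Sample Size unless noted): 100 randomised per group; 12% dropout, so n = 100 × 0.88 = 88 analysed per group; baseline-to-postoperative correlation 0.5; correlation between postoperative measures 0.7; power 80%; two-sided 5% and 2.5%; primary time point 3 months (Primary Outcome).

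**Formula.** For a baseline-adjusted comparison of the mean of m postoperative measures, in standard deviation units:

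- V = (1 + (m − 1) × 0.7)/m − 0.5²
- detectable difference d = (z₁₋α/₂ + z₀.₈₀) × √(2V/n)
- z sums: 1.960 + 0.842 = 2.802 at 5%; 2.241 + 0.842 = 3.083 at 2.5%

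**Step 1: reproduce the printed figures.** Take m = 2 (day 4-7 and 3 months averaged). V = 1.7/2 − 0.25 = 0.60 and √(2 × 0.60/88) = 0.1168. Then d = 2.802 × 0.1168 = 0.327 and 3.083 × 0.1168 = 0.360. Both printed values are matched.

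**Step 2: check the formula on the neighbouring claim.** For the biomarkers m = 4, so V = 3.1/4 − 0.25 = 0.525 and d = 2.802 × √(1.05/88) = 0.306. The plan states 0.3.

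**Step 3: apply it to the primary outcome.** Take m = 1 (3 months alone). V = 1 − 0.25 = 0.75 and √(1.5/88) = 0.1306. Then d = 0.366 at 5% and 0.403 at 2.5%.

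**Step 4: power at the printed differences, 3 months alone, one domain.**

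- 0.33 at 5%: Φ(0.33/0.1306 − 1.960) = Φ(0.568) = 71.5%
- 0.36 at 2.5%: Φ(0.36/0.1306 − 2.241) = Φ(0.516) = 69.7%
- Using the t distribution instead: 71.0% and 69.0%

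**Step 5: see whether a kinder assumption restores 80%.**

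| 3-month outcome, baseline correlation 0.5 | Power, 0.33 at 5% | Power, 0.36 at 2.5% |
|---|---|---|
| 200 randomised, 12% dropout | 71.5% | 69.7% |
| 208 randomised (Abstract), 12% dropout | 73.2% | 71.6% |
| 200 randomised, mixed model, all with day 4-7 data, 88 per group with 3-month data | 73.4% | 71.8% |
| 200 randomised, no dropout | 76.9% | 75.7% |
| 208 randomised, no dropout | 78.5% | 77.5% |

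For the mixed-model row, the correlation of the two postoperative measures given baseline is (0.7 − 0.25)/0.75 = 0.6. The variance of each group's 3-month mean is therefore 0.75 × (0.64/88 + 0.36/100) = 0.00815. The standard error of the difference is √(2 × 0.00815) = 0.1277.

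Rounding does not explain the gap either. At the top of the rounding intervals (0.335 and 0.365), power with 88 per group is 72.8% and 71.0%.

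**Step 6: size of the gap in patients, for scale only.** At V = 0.75, 80% power for 0.33 at 5% needs 109 analysed per group (218/0.88, about 248 randomised). For 0.36 at 2.5% it needs 111 per group (222/0.88, about 253 randomised).

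**The case against.** **The origin of the figures is inferred.** This stands. The article never says that two visits were averaged. A second set of inputs also fits: the superseded target of 150 (75 per group) with one postoperative measure, baseline correlation 0.7 and no dropout gives V = 0.51 and d = 0.327 and 0.360. The finding does not depend on which is true, because neither set describes 3-month cognition under the current inputs.

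**The success rule is more forgiving than one domain.** Superiority needs only one domain to succeed. If a difference of 0.36 held in two domains, power to succeed in at least one at 3 months would be about 81% to 87%, assuming test statistics correlated at 0.7 down to 0.3 (not given in the plan). This limits the finding to power per domain. However, the Sample Size section does not present its figures as power across several domains, and they do not reproduce that way. The broader description of a small to moderate target also survives, since 0.37 and 0.40 both lie between 0.2 and 0.5.

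**About 70% is the low end.** The plan says up to 12% dropout, and 208 patients were randomised. This stands in part: the shortfall narrows, but no row of the table reaches 80%.

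**Two stronger readings are tempting and not supported.**

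- A reader might infer that "The target effect size was unchanged" (Key Changes to the Protocol) is false. That comparison needs the dropout allowance of the 150-patient design, which is not given. The text says only that early dropout was higher than anticipated. With an assumed 5% to 12% allowance, one measure and correlation 0.7, that design would give 0.335 to 0.348 at 5%. The number of measures it used is not stated either. No error can be shown there.
- A reader might infer that the analysis will pool the treatment effect over both visits. Nothing in Statistical Analysis says so, and whether the model has a treatment-by-time term may properly be left to the analysis plan.

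**Conclusion.** The point holds as a numerical inconsistency within the Sample Size section, judged against the primary outcome the article declares. On the stated inputs, the differences detectable at 3 months with 80% power are about 0.37 (5%) and 0.40 (2.5%), not 0.33 and 0.36. Per-domain power at the printed differences is about 71% and 70% with the full 12% dropout, and about 77% and 76% with none.

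This rests on a normal approximation with baseline adjustment, the stated correlation of 0.5 and equal groups. The t-based check changes power by less than one percentage point. It would fail only if the primary effect were defined as the average over day 4-7 and 3 months, which the Primary Outcome section does not do. The shift is about 0.04 standard deviations. It affects how a null result is read, not the validity of the test or of the estimate.

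**What to change.** In Sample Size, restate the detectable differences for 3-month cognition as 0.37 at 5% and 0.40 at 2.5%, or state that power for 0.36 at 2.5% is about 70% per domain with 12% dropout. Say how many postoperative measures the cognitive figures use, as is already done for the biomarkers. If 0.33 and 0.36 come from the two-visit average, say that they apply only to it.

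As a clarification, confirm that the primary contrast from the mixed model is the treatment effect at 3 months, in line with the Primary Outcome section.

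The cost is a few sentences and a slightly less favourable stated sensitivity. Recruitment and follow-up are complete, so no extra patients are proposed. The sentence on the target effect size needs no change on this ground.

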### Statistical Analysis

The primary and other continuous outcomes are analyzed by regression modeling, transforming logarithmically if required, and jointly modeling baseline values where available using mixed models for repeated measures. Serial CPB oxygen delivery and utilization are compared between the 2 groups to determine whether this is improved using NIRS. Time to CICU and hospital discharge is analyzed by Cox regression.

The findings are reported as effect sizes with 95% confidence intervals. Frequencies of complications, which are too infrequent for the trial to be able to detect differences between groups, are tabulated descriptively in accordance with guidelines for reporting RCTs [53]. Analyses are based on intention-to-treat and are adjusted for center and surgery (valve or CABG and valve). For the study to conclude that the patient-specific algorithm is superior to the generic algorithm evidence of superior cognitive function for at least one domain at the 2.5% level is required (the significance level chosen to reduce the likelihood of a type 1 error, but not to be as conservative as a Bonferroni correction).

Health economic analysis are undertaken by the Health Economics Research Centre, University of Oxford. Analyses are designed and conducted to estimate the costs and likely cost of the alternative approaches identified in this protocol. These analyses help to determine whether there are likely to be improvements in patient health outcomes (such as morbidity through complications) associated with the proposed new algorithm, and whether better use can be made of scarce National Health Service (NHS) resources.

Resource use data collection are integrated, where possible, into study documentation supplemented by clinical and laboratory observational data. The analysis calculates the average cost and outcome on a per-patient basis and from this the incremental cost-effectiveness ratios for the different blood algorithms are derived, producing an incremental cost per-complication avoided. Probabilistic sensitivity analysis are used to demonstrate the impact of the variation around the key parameters in the analysis of the baseline cost-effectiveness results. This examines the impact of changing resource use in particular to help with generalizing the study results to other UK settings. The results are expressed in terms of a cost-effectiveness acceptability curve. A single analysis is performed at the completion of the study and no interim analyses and subgroup analyses are planned.

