## Introduction

### The Clinical Problem

The development of cardiopulmonary bypass (CPB) represents one of the greatest achievements of modern medicine. By maintaining adequate perfusion through an extracorporeal pump and oxygenator, CPB enables complicated surgical procedures to be performed on the heart. Since its development in the 1950s, refinement of CPB technology has made cardiac surgery safer and widened its availability to increasingly elderly and sicker patients. Perfusion technology remains imperfect, however, and CPB is still associated with significant morbidity [1]. The pathophysiology of CPB-associated morbidity is multifactorial but includes regional hypoperfusion and tissue hypoxia, often within vascular beds, which are already abnormal due to advanced age or comorbidities such as diabetes. Consequently, up to 25% of patients may experience neurocognitive decline [2] and up to 25% experience acute kidney injury [3].

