###  Aims and Objectives

We aim to compare generic and patient-specific algorithms for optimizing tissue oxygenation during CPB in adult cardiac surgery patients in a randomized controlled trial (RCT). Compared to the generic algorithm (including a hematocrit transfusion threshold of 23), we hypothesize that the patient-specific, goal-directed algorithm (based on optimizing regional cerebral oxygen saturation), combined with a prespecified “restrictive” hematocrit transfusion threshold of 18, will result in fewer RBC transfusions and will reduce complications arising from low oxygen levels during CPB. The specific objectives of this multicentre RCT are to (1) compare the effects of the patient-specific, goal-directed algorithm versus the generic algorithm in terms of cognitive function; (2) compare the effects of the patient-specific, goal-directed algorithm versus the generic algorithm with respect to a range of secondary outcomes; and (3) estimate the cost effectiveness of the patient-specific, goal-directed algorithm versus the generic algorithm and describe this in terms of a cost-effectiveness acceptability curve.

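### Every complication is assigned to descriptive tabulation as too infrequent, yet infection, and possibly acute kidney injury, may be common enough to report with effect estimates and 95% intervals

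*Protocol article*

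**What the plan says.** In the protocol article, Statistical Analysis first sets a general reporting rule: "The findings are reported as effect sizes with 95% confidence intervals". The next sentence takes complications out of it: "Frequencies of complications, which are too infrequent for the trial to be able to detect differences between groups, are tabulated descriptively". The section names regression or mixed models for continuous outcomes and Cox regression for the two discharge times. It names no model for a binary outcome. Analyses are by intention-to-treat, adjusted for center and type of surgery.

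Secondary Outcomes lists the clinical events. They include infectious complications (sepsis and wound infection) and "postoperative acute kidney injury (defined as AKIN criteria stage 1, 2, or 3"), that is, AKI of any stage.

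Two places give frequencies. Key Changes to the Protocol reports, from another transfusion trial, "92% versus 53% transfused, 25% infection rate in both groups with less than 20% due to sepsis". The Clinical Problem says of bypass patients that "up to 25% experience acute kidney injury".

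Aims and Objectives hypothesizes that the new algorithm "will result in fewer RBC transfusions and will reduce complications arising from low oxygen levels during CPB", and its second objective is to compare the algorithms on a range of secondary outcomes. The health-economic part of Statistical Analysis plans an incremental cost for each complication avoided, with probabilistic sensitivity analysis.

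**The concern.** The rule treats all complications alike and rests on their being rare. That suits stroke or death if they prove rare. It fits poorly for an outcome that may affect a quarter of patients. Infection was a co-primary outcome when the trial was designed. AKI counts any AKIN stage and bears on the stated aim of preventing organ injury.

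Followed as written, the report would give counts by arm for these two outcomes and no estimate of the difference or its uncertainty. The arms differ in hematocrit transfusion threshold (18 against 23), so a reader will want to know how large a benefit or a harm the data can exclude. Bare counts do not say. The economic analysis, meanwhile, needs a difference in complications between arms and its uncertainty, so that difference would be used for cost-effectiveness but not reported clinically.

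**Working it through.** **Inputs.** From Sample Size: "with 80% power and 5% significance (two tailed), 200 patients (100 per group) are recruited", up to 12% dropout (100 × 0.88 = 88 per group), and correlations of 0.5 (baseline to post) and 0.7 (post to post). Event rates: 25% is taken as an assumed control rate from the two background figures, with 15% as a lower alternative.

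**The plan's own figure.** The article gives no power figure for any complication, so the check on method uses the cognitive outcome. With two postoperative measures averaged and adjusted for baseline, the variance factor is (1 + 0.7)/2 − 0.5² = 0.60. The detectable standardized difference is (z for α + z for power) × √(2/88) × √0.60:
- at 5%: (1.960 + 0.842) × 0.1508 × 0.7746 = 0.327 (stated 0.33);
- at 2.5%: (2.241 + 0.842) × 0.1508 × 0.7746 = 0.360 (stated 0.36).

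Both reproduce, so 88 to 100 per group is the right range to carry forward.

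**Expected events.**
- 25%: 0.25 × 200 = 50, or 0.25 × 176 = 44.
- 15%: 0.15 × 200 = 30, or 0.15 × 176 ≈ 26.

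**Power from a 25% control rate** (two proportions, pooled variance under the null, two-sided 5%, no continuity correction). For 25% against 15% with 100 per group:
- null standard error √(2 × 0.20 × 0.80/100) = 0.0566;
- alternative standard error √((0.1875 + 0.1275)/100) = 0.0561;
- z = (0.10 − 1.96 × 0.0566)/0.0561 = −0.19, so power is 42%.

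| Comparison | Power, 100 per group | Power, 88 per group |
|---|---|---|
| 25% v 20% | 13% | 12% |
| 25% v 17.5% | 25% | 23% |
| 25% v 15% | 42% | 38% |
| 25% v 12.5% | 62% | 57% |
| 25% v 10% | 80% | 75% |

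Power of 80% needs a fall to 10.0% (100 per group) or 9.2% (88 per group). In the direction of harm it needs a rise to about 44% or 45%. From a 15% control rate, it needs a fall to about 3.5% or 3.0%.

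**Interval if both arms have the same rate**, 1.96 × √(2p(1 − p)/n):
- p = 25%: 1.96 × √(0.375/100) = 0.120; 1.96 × √(0.375/88) = 0.128.
- p = 15%: 1.96 × √(0.255/100) = 0.099; 1.96 × √(0.255/88) = 0.106.

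So the interval would be about ±12 to 13 points at 25%, and ±10 to 11 points at 15%.

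**The case against.** The best defense is that the sentence is about power. It says complications are too infrequent to detect differences, and at 25% that is largely true: only about a 60% relative reduction (25% to 10%) reaches 80% power. This stands. A reader might infer that the stated reason is simply false, or that the trial could test these outcomes properly. The figures do not support that. What they question is the label of infrequency, and whether low power justifies giving no interval.

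Other points also stand, and they limit the concern:
- Neither 25% is a planning rate. The AKI figure is an upper bound for bypass patients generally, and the infection figure comes from a trial of postoperative thresholds. The exclusion criteria and the restriction on post-discharge sepsis could lower the rates here.
- A reader might infer that two hypothesized effects go unestimated. The hypothesis concerns complications of low oxygen. Infection was linked to transfusion, and was demoted after the other trial found equal rates.
- A reader might infer that nothing inferential will be said about kidney injury. Renal biomarkers are collected serially, and continuous outcomes are modeled with intervals. The gap is the binary AKI outcome.
- The cost-effectiveness analysis implies some between-group difference in complications, and anyone could derive a crude one from the tabulated counts.

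One could add that models for secondary binary outcomes usually belong in the analysis plan, which is not shown. That does not answer the point, because the article states a rule and a reason for it. If the sentence was meant to cover only those complications that are too rare, it does not say so: as punctuated, it describes the whole class.

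**Conclusion.** The concern holds in a limited form. The article applies one descriptive rule to all complications, while its own background figures suggest that infection, and possibly AKI of any stage, will not be rare. About 50 events in 200 patients at 25%, or 30 at 15%, are enough to estimate a difference, though not precisely. An interval of roughly ±10 to 13 points would show the reader that imprecision and how much benefit or harm remains possible. Leaving it out departs from the plan's general reporting rule, and fits poorly with the second objective and with the cost per complication avoided.

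The result rests on assumed control rates of 15% to 25% and on 88 to 100 patients per group. It is not a claim that the trial is powered for these outcomes, and it does not touch the primary conclusion on cognition.

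**What to change.** Limit descriptive-only tabulation to complications that prove rare, and say how that will be judged. For infectious complications and binary AKI (any AKIN stage), report a risk difference and an odds or risk ratio with 95% intervals, by intention-to-treat and adjusted for center and planned surgery, as the plan already does elsewhere. Label them as secondary estimates and state that the trial was not powered for them.

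The cost is two extra secondary models on data already collected, with no change to trial conduct. The intervals will be wide, and the text should say so, so that an inconclusive result is not read as evidence of no difference.
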